### Outcomes

3.3

The primary outcome of the study is adherence to neurology clinic appointments. This is defined as the number of appointments attended as scheduled and on time by the participant, as reported by the investigator.

Secondary outcomes are as follows:
Percent of PWE who achieve seizure freedom.Seizure frequency reduction: The percentage decrease in number of monthly seizures from baseline to the study endpoint of 360 days.

A complete list of outcomes can be found in Table 2.

**TABLE 2 epi412889-tbl-0002:** Primary, secondary, and exploratory outcomes of interest.

Outcome category	Outcome	Definition	Method of measuring
Primary	Adherence to Neurology Clinic Appointments	The number of appointments attended as scheduled and on time by the participant	Investigator reported
Secondary	Seizure freedom	% of PWE who achieve seizure freedom, or the ability to live without seizures of any type	Seizure diary counts
Secondary	Seizure frequency reduction	The percentage decrease in the number of monthly seizures from baseline to the study endpoint of 360 days	Seizure diary counts
Exploratory	Quality of life in epilepsy	A standardized scale and subjective report of physical, social, and psychological well‐being by a person with epilepsy	Patient/parent reported
Exploratory	Number of visits to traditional healers	Self‐reported number of visits to non‐allopathic providers for epilepsy management	Patient reported
Exploratory	Self‐reported adherence to ASMs	The number of pills left in the medication bottle, determined as a medication possession ratio	Investigator Counted
Exploratory	Stigma scale in epilepsy	A standardized scale and subjective report of stigma perceived by a person with epilepsy	Patient reported
Exploratory	Days attended at work or school	Self‐reported days attending school or work by a person with epilepsy of the past 90 days	Patient reported
Exploratory	Number of unintentional injuries due to seizures	Including burns, fractures, head injury, and related injuries in the past 90 days	Patient reported
Exploratory	Number of status epilepticus events	Reported by participant and family member in a log, articulating a seizure episode lasting >5 min	Patient reported

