### Trial design

1.1

A randomized, double‐blinded clinical trial will be performed, including multiple healthcare facility sites in rural and urban Guinea but headquartered at the Ignace Deen Hospital in the capital city, Conakry. Two hundred PWE, clinically diagnosed by a Guinean and a U.S. neurologist, ages 18 years and above, will be enrolled and randomized 1:1 to (i) education and medication, or (ii) education and CCT (Figure 1). All participants will receive epilepsy education. Participants will be interviewed and examined by the Guinean–U.S. study team of neurologists at each visit. Follow‐up visits every 90 days until day 360 (approximately 1 calendar year) will assess the intervention on participants' clinical and socioeconomic outcomes. The recurring 90‐day follow‐up visits are considered beneficial to participants who may not access epilepsy care in any other way while also providing a sufficiently long timeline to study the sustainability of this intervention.

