### Objectives

1.2

The primary objective is to implement and test a novel strategy to improve outcomes across the epilepsy care cascade marked by (1) retention in epilepsy care, (2) adherence to ASMs, and (3) seizure reduction with the measured goal of seizure freedom.

The first aim is to compare free ASMs vs. conditional cash using the epilepsy cascade of care. We hypothesize that the provision of free medication versus conditional cash will lead to (1) similar retention in epilepsy care—90% of PWE—at 360 days (Hypothesis 1a), (2) 80% of PWE regularly taking ASMs at 360 days (Hypothesis 1b), and (3) 65% of PWE achieving seizure freedom 360 days postenrollment (Hypothesis 1c).

The secondary aim is to detail facilitators and barriers to free medication versus conditional cash to improve seizure freedom among PWE. We hypothesize that barriers and facilitators to the uptake of each intervention strategy can be learned through careful, structured documentation by healthcare workers during study visits using an investigator‐designed written intake form as well as free‐text responses, serving as foundational information for a future larger‐scale implementation study in low‐resource populations.

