### Intervention description

3.2

The education intervention will be given to each participant upon study enrollment in the form of a prerecorded, standardized video, made by the investigators, lasting approximately 30 min. The video is designed for people with low literacy and will answer the following basic questions: [What is a seizure? What is epilepsy? Why does epilepsy occur? Why is epilepsy a brain disorder? What works to treat epilepsy? What does not work to treat epilepsy? Why are ASMs important?] The video will be available in local languages (Sousou and Malinké), English, and French and shown on electronic tablets. A question‐and‐answer period, led by the study neurologists, will follow with no limitations on the amount of time. A flyer providing basic, written information on the education intervention will be given.

ASMs will be provided free of charge and prescribed for the participants in the study arm that includes the medication intervention. The ASM choice will be determined at the discretion of the neurologist in the context of the patient's history. There is no one best ASM for all patients, and most ASMs provide similar efficacy but dissimilar side effects and safety. There will be a total of seven possible ASMs to be used.

CCT will be conditioned on the return for follow‐up visits to the outpatient epilepsy clinic for scheduled appointments (±7 days every 90 days). Each visit for those in the CCT groups will entail the provision of 15 USD (given in the equivalent of Guinean Francs) to participants. This amount is anticipated to be a “nudge” (i.e., mildly incentivizing) as it exceeds the general cost of transportation for a return visit in the area (~5 USD on average) and ASM (which approximately costs ~4–10 USD for a monthly dosage in Guinea).^11^ It is important to note that this nudge will ensure participants in the CCT arm can afford the ASM, which enables study staff to assess outcomes from behavioral change rather than affordability considerations. The transfer will also be conditional on presence at visits, not on seizure outcomes. This ensures that participants are not penalized for aspects of their illness that are beyond their control.

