### Who will be blinded?

4.1

Participants will be blinded to the primary study hypothesis. The Guinean site collaborators providing the intervention will be blinded to the primary study hypothesis.

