## STATISTICAL METHODS

6

We choose a randomized two‐arm design with an equal sample size in the arm with the provision of conditional cash and the arm with the provision of free medication. Our sample size calculation is based on Hypothesis 1a.

To investigate Hypothesis 1a, we will first test the null hypothesis that the retention rate of the group with the provision of conditional cash is less than or equal to 90% using a non‐inferiority one‐sample proportion test. We will then test the null hypothesis that the provision of conditional cash will lead to a retention rate no less than the retention rate of free medication (controlling for medication type) using a noninferiority two‐sample proportion test. Since there are two hypotheses, in the sample calculation, we applied the Bonferroni correction to ensure a familywise error rate of 0.05.^27^ Given the existing studies and preliminary results, we expect that the retention rate of the group with the provision of conditional cash will have a retention rate higher than 90%. This reflects financial incentive clinical trials in other diseases where the intervention improves retention in care, particularly studied in HIV/AIDS.^28^, ^29^

Assuming it is 90%, to ensure a statistical power of 80%, with a noninferiority margin of 8.5%, the sample size of the arm with the conditional cash required is 98.^30^ We will then test the null hypothesis that the provision of conditional cash will lead to a retention rate no less than the retention rate of free ASMs using a noninferior two‐sample proportion test. Assuming the conditional cash group has 90% of PWE who will return at 12 months, with a noninferiority margin of 12%, to ensure statistical power of 80%, the sample size of the arm with the conditional cash required is 99.

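### The declared primary outcome (a count of on-time appointments) is not the variable that Hypothesis 1a, its two non-inferiority tests and the sample size use (the proportion retained at 360 days)

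*Protocol article*

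**What the plan says.** All references are to the protocol article.

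- **Section 3.3 (Outcomes):** "The primary outcome of the study is adherence to neurology clinic appointments". The next sentence gives the scale: "This is defined as the number of appointments attended as scheduled and on time by the participant, as reported by the investigator". Table 2, which the section presents as the full outcome list, repeats this definition in its single primary row.
- **Section 1.2 (Objectives):** the first hypothesis is "similar retention in epilepsy care—90% of PWE—at 360 days (Hypothesis 1a", a percentage of people at one time point.
- **Section 6 (Statistical methods):** "Our sample size calculation is based on Hypothesis 1a". Two tests are planned, a one-sample and a two-sample non-inferiority test of proportions, both on a retention rate. For the two-sample test the assumption reads "Assuming the conditional cash group has 90% of PWE who will return at 12 months". The margins are 8.5% and 12%, the power is 80%, and the cash-arm sizes are 98 and 99.
- **Section 6, last paragraph:** a generalized linear mixed model is planned for the observations at days 90, 180, 270 and 360, with the intervention among the covariates. No response variable is named.
- **Section 5.2:** participants may attend within 7 days either side of the scheduled date, with no restriction by arm.

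**The concern.** The primary outcome section and the statistical section describe two different variables. One is a count of visits made on time; the other is a yes/no status at the end of follow-up. No rule converts the first into the second, and the second is missing from the outcome table.

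The two can rank the same people in opposite order. Someone who attends on time at days 90, 180 and 270 but not at day 360 scores 3 and is not retained. Someone who attends only at day 360 scores 1 and is retained.

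Two things are at stake. The same data could yield two different results, each with a claim to be the primary one. And the 80% power is not a statement about the outcome that the article calls primary.

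**Working it through.** **1. Inputs from section 6.** Assumed retention 0.90; margins 0.085 (one-sample) and 0.12 (two-sample); power 0.80; familywise error 0.05 with Bonferroni correction over two hypotheses, hence 0.05/2 = 0.025 each, taken as one-sided. (1.960 + 0.842)² = 7.849.

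**2. Reproducing the stated sizes.**

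- One-sample: n = p(1−p) × 7.849 / margin² = 0.09 × 7.849 / 0.085² = 97.8, rounded up to **98**. This matches.
- Two-sample: n per arm = 2p(1−p) × 7.849 / margin² = 0.18 × 7.849 / 0.12² = 98.1, rounded up to **99**. This matches.

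Other error levels do not match: one-sided 0.05 gives 78 and 78, and 0.0125 gives 119 and 119. At 100 per arm the power is 80.9% (one-sample) and 80.7% (two-sample). The sizing is sound, and it is for a binary outcome.

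**3. Side by side.**

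| | Declared primary outcome (section 3.3, Table 2) | Variable tested and sized (sections 1.2 and 6) |
|---|---|---|
| Unit | Appointments per participant | Participants |
| Scale | Count (0 to 4 if the four follow-up visits are counted) | Retained or not |
| Time | All follow-up visits | Day 360 / 12 months |
| Test | None assigned | Two proportion tests |
| Margin | None | 8.5% and 12% |
| Power | None | 80% |
| Listed in Table 2 | Yes | No |

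**4. What the power for the count would be.** The article gives no mean, standard deviation, within-person correlation or margin for the count, so these are assumptions: four visits, on-time probability p = 0.90 per visit, intraclass correlation (ICC) from 0 to 1, no true difference, one-sided 0.025.

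SD = √[4p(1−p)(1 + 3·ICC)], which is √0.36 = 0.60 at ICC 0 and √1.44 = 1.20 at ICC 1. Then n per arm = 2·SD² × 7.849 / margin².

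| Margin (visits) | n per arm, ICC 0 to 1 | Power at 100 per arm, ICC 0 to 1 |
|---|---|---|
| 0.48 (12% of 4) | 25 to 99 | above 99% to 81% |
| 0.25 (assumed, tighter) | 91 to 362 | 84% to 31% |

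The result depends on a margin and a correlation that the article does not supply.

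**The case against.** The strongest reply is that little is lost in practice. Carry the article's own 90% and 12% over to the count and the planned size is adequate at every correlation (81% power or more). The mixed model could also be fitted to attendance at each visit. Both points are right and they limit the finding. The model paragraph, however, names no response, effect measure or margin, so it is not a stated primary analysis, and the carry-over of the margin is ours, not the article's. Nor is this detail that a fuller analysis plan would normally supply: such a plan can add to the two sections but cannot make both true as they stand.

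Four stronger readings are tempting and not supported.

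- *The trial is underpowered for its primary outcome.* The low figures need a tighter margin or lower attendance than the article assumes.
- *The 90% assumption cannot fit the count.* It can: 90% per visit gives a mean of 4 × 0.9 = 3.6, which is 90% of appointments. An outcome requiring all four visits on time would behave differently, but none is declared.
- *The on-time rule biases the result towards cash.* The payment is conditioned on "visits to the outpatient epilepsy clinic for scheduled appointments (±7 days every 90 days", but section 5.2 gives everyone the same window, and higher attendance under payment is the effect being tested.
- *Unmasked reporting distorts the outcome.* Attendance on a date is largely objective, and the article shows no route by which it would be misrecorded.

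**Conclusion.** The contradiction stands. The only declared primary outcome is a count with no assigned test, margin or power. The variable that carries the hypothesis, both non-inferiority tests and the 98 and 99 per arm is binary retention at 360 days, which the outcome table omits. This rests on the article's wording and on the exact reproduction of both sizes; it does not depend on the assumptions made for the count. Those show only that the power for the count is undetermined, neither adequate nor inadequate. The matter should be settled before any outcome data are analysed.

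A separate, minor point of wording: section 1.1 calls the study a double-"blinded clinical trial will be performed, including multiple healthcare facility sites in rural and urban Guinea", whereas section 4.1 says "Participants will be blinded to the primary study hypothesis" and says the same of the site collaborators who deliver the intervention. What is masked is the hypothesis, not the allocation.

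**What to change.** Make sections 1.2, 3.3 (with Table 2) and 6 name the same primary variable.

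**Cheapest route.** Declare the binary outcome already sized: attended the day-360 visit within the ±7-day window that section 5.2 gives all participants, with everyone randomised in the denominator. State that the 90% assumption refers to attendance so defined. Move the on-time count to the secondary outcomes and analyse attendance by visit in the planned mixed model, named there as the response. Tests, margins and sample sizes stay as they are. The cost is wording, plus a real if modest loss: the count gives up its primary label, and the first three follow-up visits leave the primary outcome.

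**Alternative.** Keep the count as primary and state its test, its margin in visits, its assumed standard deviation and the resulting power; restate Hypothesis 1a to match. The cost is a new sample-size justification, which may or may not support 200 participants.

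Neither route needs new data. Separately, replace the double-blind label with a statement that participants and site collaborators are masked to the primary hypothesis only.

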The Guinea Epilepsy Project, a prospective observational cohort study, began in 2017 by the Guinean and U.S. neurologist authors, has enrolled several 100 PWE to date.^11^, ^12^, ^13^, ^14^, ^15^ Several negative consequences of untreated and undertreated epilepsy have been observed including unintentional death; missed opportunities for school attendance of Guinean children with epilepsy^12^; poor cognitive performance; frequent unintentional injuries; epilepsy stigma^16^; high rates of traditional healing injuries including cuttings, instrumentation, and animal sacrifices^11^; and large losses of personal wealth on ineffective treatment options.^17^ Similar to other low‐resource locations, a high number of PWE do not take ASMs and have suffered serious consequences as a result, including death from unintentional injury or status epilepticus.^13^

As a response to this tragic situation, the study team proposes to compare two ways to deliver epilepsy care to people with epilepsy (PWE) in a low‐income setting. Although several lines of evidence suggest that both these interventions will lead to improved outcomes,^18^, ^19^, ^20^ they have not been directly tested in low‐resource populations with low literacy. *Conditional cash transfer* (CCT) interventions in particular have not been systematically tested in PWE or in people with any chronic neurological disorder. CCT interventions grant individuals a sum of money on the condition that they fulfill a predetermined task. In this way, CCT interventions create a “nudge,” or an economic incentive, for taking a desired course of action. These interventions differ notably from *unconditional cash transfer* (UCT) interventions, which simply provide direct payment to individuals without any behavioral nudges. As such, CCT interventions uniquely serve as an important lever for both alleviating the financial burden of poverty and incentivizing people to act for the benefit of their own health.

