### Participant timeline

3.4

The timeline of screening, enrolment, and interventions is provided in Table 3. The interventions will be provided at follow‐up visits taking place every 90 days. The baseline visit will include a neurologist's description of seizure history, including seizure semiology, epilepsy diagnosis, and etiology of epilepsy to the degree possible given resource limitations. Structured forms will be used. Several measures will be collected during follow‐up visits, including detailed seizure information, quality of life surveying, medication possession, stigma scale surveying using the Stigma Scale of Epilepsy (SSE),^26^ health visit history, school/work attendance, and injury surveying.

**TABLE 3 epi412889-tbl-0003:** Schedule of tests and events at each study visit.

	Screening	Baseline	90	180	270	360
Study visit		1	2	3	4	5
Informed consent	×					
Assess inclusion and exclusion criteria	×	×				
Medical history	×	×				×
Seizure diary		×	×	×	×	×
Concomitant medication history		×		×		×
Quality of Life in Epilepsy‐31 scale		×	×	×	×	×
Consumption and household assets module		×				×
Stigma Scale of Epilepsy		×	×	×	×	×
Medication possession ratio, as appropriate based on assigned arm			×	×	×	×
Health visit history (allopathic and traditional)		×	×	×	×	×
School/work attendance log		×	×	×	×	×
Injury survey		×	×	×	×	×
Status epilepticus query		×	×	×	×	×
Body weight, height, heart rate		×				×
Urine pregnancy test (for people of childbearing potential), *as needed	×	*	*	*	*	*
Clinical labs (including serum Na+, glucose), *as needed	*	×	*	*	*	*
Brain MRI	×					×
Conditional cash allocation, as appropriate based on assigned arm		×	×	×	×	×
Vitality status assessment			×	×	×	×

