For Hypothesis 1b, we will use a one‐sample proportion test to test the null hypothesis that the percentage of PWE regularly taking ASMs at 12 months in the conditional cash arm is less than or equal to 85%, and we will use a two‐sample proportion test for the null hypothesis that the percentage of PWE regularly taking ASMs in the conditional cash arm is less than or equal to the percentage of PWE regularly taking ASMs in the free medication arm. For Hypothesis 1c, we will use a one‐sample proportion test to test the null hypothesis that the percentage of PWE with seizure freedom at 12 months in the conditional cash arm is less than or equal to 65%, and we will use a two‐sample proportion test for the null hypothesis that the percentage of seizure freedom in the conditional cash arm is less than or equal to the percentage of seizure freedom in the free medication arm.

To leverage the longitudinal observations collected during follow‐up visits at 90, 180, 270, and 360 days, we will use a generalized linear mixed effects model which allows us to study the association between multiple baseline variables (e.g., including the intervention options, education level, medication status, ASM type, distance to the study clinics) while accounting for the correlation between longitudinal observations.

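### Table 2 rests both seizure outcomes on diary counts alone, although seizures are also asked about at every visit; for seizure freedom, missed entries can only err towards success against the fixed 65% benchmark

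*Protocol article*

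**What the plan says.** Section 3.3, Table 2, defines seizure freedom as the share "of PWE who achieve seizure freedom, or the ability to live without seizures of any type". The method column reads "Seizure diary counts", both for this outcome and for seizure frequency reduction. The same table names a second observer for status epilepticus, an exploratory outcome: "Reported by participant and family member in a log".

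Other seizure information is gathered. Section 1.1 states: "Participants will be interviewed and examined by the Guinean–U.S. study team of neurologists at each visit". Section 3.4 adds: "Several measures will be collected during follow‐up visits, including detailed seizure information". Table 3 schedules the diary at baseline and at days 90, 180, 270 and 360. Nothing links the interview or the additional seizure information to the two seizure outcomes.

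Section 1.2 sets the target as "65% of PWE achieving seizure freedom 360 days postenrollment (Hypothesis 1c"). Section 6 then sets up a one-sample test whose null is worded as "the percentage of PWE with seizure freedom at 12 months in the conditional cash arm is less than or equal to 65" per cent, and adds a two-sample comparison with the free-medication arm.

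On the population, the Introduction says of the two interventions that "they have not been directly tested in low‐resource populations with low literacy", and section 3.2 describes an education video made for people with low literacy.

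**The concern.** A diary count fails in two ways. The patient cannot enter a seizure that he or she did not notice, and a seizure that was noticed may not be written down. A diary handed in blank does not show which of these happened, or whether there were no seizures.

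For seizure freedom the error has one direction. If every seizure is missed, a participant who is not seizure-free is scored as free; missed entries never turn a free participant into one who is not. The one-sample test is the most exposed, because it compares the cash arm with a fixed number and randomisation gives no protection. In the two-sample test, equal under-recording shrinks a true difference and unequal under-recording creates a false one.

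Section 1 calls seizure freedom the outcome that people with epilepsy value most. Entries not made during follow-up cannot be reliably recovered later, so the source has to be settled before data collection.

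**Working it through.** **Plan's own figures.** The article gives no sample size or power for seizure freedom. Its figures of 98 and 99 concern retention. They reproduce at one-sided 0.025: (1.960 + 0.842)² × 0.9 × 0.1 / 0.085² = 97.8, so 98, and the two-sample formula with a 12% margin gives 99. They do not bear on this point.

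**Inputs.** Cash arm n = 100 (200 randomised 1:1, section 1.1). Benchmark 65% (sections 1.2 and 6). No significance level is stated for Hypothesis 1c, so one-sided 0.05 is assumed and 0.025 is shown beside it. The share m of participants with continuing seizures who are scored as free is an assumption.

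**Apparent rate.** With true rate p, the apparent rate is p + m(1 − p). At p = 0.65 this is 0.65 + 0.35m.

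**Rejection rule.** Under 65%, P(X ≥ 73) = 0.056 and P(X ≥ 74) = 0.035, so the exact one-sided 0.05 test rejects at 74 or more. At one-sided 0.025 it rejects at 75 or more (actual size 0.021).

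**False success when the true rate is exactly 65%:**

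| m | Apparent rate | Reject at ≥ 74 | Reject at ≥ 75 |
|---|---|---|---|
| 0 | 65.0% | 3.5% | 2.1% |
| 5% | 66.8% | 7.4% | 4.8% |
| 10% | 68.5% | 14.0% | 9.6% |
| 20% | 72.0% | 37.5% | 29.3% |

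**If the true rate is 60%** (one-sided 0.05), the chance of rejection is 0.2% with no under-recording, 2.2% at m = 10% and 11.8% at m = 20%. The apparent rate reaches 65% at m = (0.65 − 0.60)/0.40 = 12.5%.

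**Two-sample test** (100 per arm, one-sided 0.05; all rates assumed). Equal under-recording multiplies the true difference by (1 − m). With 65% v 45%, power falls from 89% to 83% at m = 10% and 76% at m = 20%. For unequal under-recording, take a true 60% in both arms with m = 20% (cash) v 10% (free medication). The apparent rates are 0.60 + 0.20 × 0.40 = 68% and 0.60 + 0.10 × 0.40 = 64%, and the chance of wrongly finding cash better is about 15%.

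**Schooling** (Table 1, adult column): 19 + 30 + 26 + 29 + 44 = 148 classified. No school or primary only is 49/148 = 33%; no school is 19/148 = 13%; university is 44/148 = 30%.

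**The case against.** A reader might infer that an unkept diary is scored as zero and counted as success. The article does not say so. Section 5.1 says that missing data will be addressed and that nothing will be imputed, which points to an unreturned diary staying missing. That leaves the diary that is returned blank or incomplete, which is not recognisable as missing, and the seizure nobody noticed.

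It can be argued that reconciling diary and interview is an operational detail for the full protocol or analysis plan, neither of which is shown. This has force for the detailed scoring rule. It does not remove the point, because Table 2 states the method and, for status epilepticus, names a family observer. The choice of source is in the text.

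The interviews are a real safeguard, and the diary may well be reviewed with staff. But the article does not make what the interview finds part of the outcome.

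The literacy argument should not be pressed. A third of the prior cohort's adults had at most primary schooling, but 30% had university education, and primary schooling is not inability to record a count. Unnoticed seizures do not depend on schooling.

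The size is not known. A participant is misclassified only if every seizure is missed, and adults in the prior cohort averaged 2.8 seizures in the past month, so large shares would be extreme.

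It is also tempting to say that seizure frequency reduction is inflated in the same way. It is a percentage change from baseline, so proportionate under-recording at both times cancels. It is inflated only if recording worsens after baseline, which the article gives no reason to assume.

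**Conclusion.** The point holds in limited form. Table 2 names diary counts as the only source for seizure freedom and seizure frequency reduction, while better information is collected at the same visits and left unconnected. For seizure freedom the resulting error favours success, and the comparison with 65% cannot absorb it. With 100 participants, a true rate of 65% and an exact one-sided 0.05 test, under-recording shares of 5%, 10% and 20% raise false success from 3.5% to 7%, 14% and 38%; at 0.025 the pattern is the same. The shares are illustrative and have no source in the document. The outcome is secondary and the sample size rests on retention, so this should be corrected but does not threaten the primary analysis.

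**What to change.** In Table 2, change the method for both seizure outcomes to: seizure diary reconciled at each visit with the existing neurologist interview of the participant and, where available, a family witness. State the rule with it:

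- A seizure reported by any source counts as a seizure.
- A blank or unkept diary counts as seizure-free for that interval only if the interview covering it is negative.
- Otherwise the interval is missing, not zero. A sensitivity analysis counts such participants as not seizure-free; section 5.1's statement on imputation should allow for this.
- The rule is identical in both arms.

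The cost is wording in Table 2 and one extra item on the visit form, with no new visits or staff. The seizure-freedom percentage will be slightly less favourable, and witness report remains imperfect.
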